### Adherence and therapeutic expectations

The pharmacy personnel will monitor adherence by counting remaining pills. The success of blinding will be evaluated using a therapeutic expectations questionnaire administered at 3 and 12 months post-RP.

### Sample size calculation

Sample size analysis was done using a two-sample t-test for a log-normal geometric mean ratio with a two-sided significance level of 0.05, assuming equal variances. Based on published data [28, 29], we assume a coefficient of variation of 0.4. In the study conducted by Aronson et al. [28], a statistically significant reduction of 32% in the proportion of cells expressing Ki-67 was observed in a group receiving a low-fat diet supplemented with fish oil compared to a control group assigned to a Western diet. We determined that, for the primary outcome, a total of 126 patients (63/group) will provide 90% power [69, 70] to detect a mean ratio of the proportions of cancer cells expressing Ki-67 of ≤0.8, i.e. a 20% difference across groups. We estimate ≤3% drop out before RP (occurring in ≤1% at our institution). Based on these estimation, the sample size needed for the trial will be 130 patients (65/group).

Twelve months after RP, we expect a 5 to 10% loss to follow-up, which will affect only secondary outcomes. In absence of published data on the effects of omega-3 supplementation on inflammation mediators, we used Cohen’s *d* to calculate effect sizes [71]. A total sample size of 116 will provide 80% statistical power to detect a moderate or large effect size (≥0.5). This sample size will also be sufficient to detect expected between-groups differences on quality of life dimensions. Indeed, LCn3 supplementation reduced anxiety by 20% (d = 0.51) in one study [51] and it yielded a moderate effect size (d = 0.61) for treating depressive disorders (vs. placebo) in another [72]. For these effect sizes in our final sample, we evaluate a power of 80% to detect an effect for anxiety and a power of 92% to detect an effect for depressive symptoms.

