### Statistical analyses

#### Primary outcome

The average proportion of cells expressing Ki-67 in each group will be compared, using the t-test, after transformation of the data if the population is not normally distributed. The Wilcoxon rank sum test will be used if observations are not normally distributed after transformation procedures. Multivariable linear regression will be carried out in the event of unbalanced distributions of important baseline characteristics such as cancer grade and stage, age, baseline inflammatory levels, diet or health behaviors. The intervention leading to the primary outcome is of a relatively short duration (4–10 weeks) and since almost all recruited patients are expected to undergo prostatectomy, few missing data are expected. The analyses will include all randomized patients for whom a ki-67 is measurable.

A *per protocol* analysis will also be carried out as exploratory analyses. These analyses will include participants with a measurable ki-67 and who will have taken at least 80% of intervention or placebo doses.

For all analyses, bilateral *p*-values of less than 0.05 will be considered statistically significant.

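### 116 patients give 76% power at d = 0.5, not the stated 80%, and the anxiety and depression power figures fit about 124 patients, not 116

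*Protocol article*

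**What the plan says.** All of the statements at issue are in the second paragraph of the protocol article's Sample size calculation section.

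- Attrition at twelve months after surgery: "we expect a 5 to 10% loss to follow-up, which will affect only secondary outcomes".
- Inflammation mediators, for which the article says no published effect was available and Cohen's d was used: "A total sample size of 116 will provide 80% statistical power to detect a moderate or large effect size (≥0.5").
- Quality of life: the same sample size is said to suffice. The effect sizes come from two cited studies: "LCn3 supplementation reduced anxiety by 20% (d = 0.51) in one study" and "it yielded a moderate effect size (d = 0.61) for treating depressive disorders (vs. placebo) in another".
- Resulting power: "For these effect sizes in our final sample, we evaluate a power of 80% to detect an effect for anxiety and a power of 92"% for depressive symptoms. That sentence refers to the final sample but gives no number for it.

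The first paragraph of the section sets 126 patients (63 per group) for the primary outcome and 130 (65 per group) after allowing up to 3% dropout before surgery. The Statistical analyses section applies a two-sided 5% level to all analyses.

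**The concern.** Every input needed to check the first figure is printed: total sample size, allocation, significance level, sidedness and effect size. Together they do not give 80%. The anxiety and depression figures also look too high for 116 patients, although the paragraph presents that sample size as the one that suffices for quality of life.

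What is at stake is how a null secondary result is read. By the stated power, the chance of missing a true d = 0.5 is 20%. For an unadjusted comparison in 116 patients it is about 24%. A reader who wants to know what the twelve-month comparisons can exclude needs the correct figure and the sample size it belongs to.

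**Working it through.** **Inputs.** Two-sided alpha 0.05 (Sample size calculation; Statistical analyses). Allocation 1:1 (Randomization/concealment/blinding). Total 116, so 58 per group. Effect sizes d = 0.5, 0.51 and 0.61 (Sample size calculation).

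**Method.** For n per group, the noncentrality is δ = d·√(n/2) with 2n − 2 degrees of freedom. Power is the probability that a noncentral t variable exceeds the two-sided 5% critical value. The normal approximation is Φ(δ − 1.96).

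**Check of the method on the primary outcome.** With a coefficient of variation of 0.4, the SD on the log scale is √ln(1.16) = 0.385. A ratio of 0.8 is a log difference of 0.223. With 63 per group, power is 89.7% (t) or 90.2% (normal), against 90% stated. The plan's primary figure reproduces.

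**Power at d = 0.5 with 116 patients.**
- δ = 0.5 × √29 = 2.693.
- Power is 76.1% (t), or Φ(2.693 − 1.96) = Φ(0.733) = 76.8% (normal), against 80% stated.
- Variants: a one-sided test gives 85%; the Wilcoxon test (efficiency 0.955) gives 74%; 116 per group gives 97%. None gives 80%.
- Sample size for 80% at d = 0.5: 64 per group, 128 in total (t), or 63 per group, 126 in total (normal).
- Effect detectable with 80% power at 58 per group: d = 0.525 (t).

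**Anxiety and depression: which sample size fits?** Power by t, with the normal approximation in brackets:

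| Total patients | Source | Anxiety, d = 0.51 (80% stated) | Depression, d = 0.61 (92% stated) |
|---|---|---|---|
| 116 | named in the paragraph | 77.7% (78.4%) | 90.3% (90.7%) |
| 117 | 130 less 10% | 78.1% (78.8%) | 90.5% (91.0%) |
| 123.5 | 130 less 5% | 80.3% (80.9%) | 92.0% (92.4%) |
| 126 | number planned at surgery | 81.1% (81.7%) | 92.5% (92.8%) |
| 130 | no loss | 82.3% (82.8%) | 93.2% (93.5%) |

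Solving in the other direction, 80% at d = 0.51 and 92% at d = 0.61 each need 62 per group by t (124 in total) and 61 per group by the normal approximation (122 in total). Both figures therefore point to the same sample of about 122 to 124.

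**Tissue mediators.** These are measured in the prostatectomy specimen, so twelve-month loss does not apply. With 126 patients, power at d = 0.5 is 79.5% (t) or 80.1% (normal).

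**What baseline adjustment could add.** The article states no correlation, so these values are assumptions. With 116 patients and d = 0.5, a correlation between baseline and outcome of 0.2 gives 77.8%, 0.3 gives 79.9%, 0.4 gives 83.0% and 0.5 gives 86.9%.

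**The case against.** The strongest defence is that a plain t-test may understate power for the blood mediators and quality of life. These are assessed relative to baseline and analysed with linear mixed models over several visits, and a modest baseline correlation of about 0.3 would bring 116 patients to 80% at d = 0.5. That is a fair reason not to overstate the consequence. It does not rescue the sentence: the article claims no such gain, and the tissue mediators have no baseline measurement and are compared by t-test or Wilcoxon test.

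A second defence is rounding, since 116 patients do give 80% power at d of about 0.525. But the same paragraph distinguishes 0.51 from 0.5, so it treats the second decimal as meaningful.

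Two stronger readings are tempting, and the document supports neither.

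- A reader might infer that the anxiety and depression figures ignore the planned loss to follow-up, or were computed on the number at surgery. The table shows otherwise. They match best at 130 less 5%, inside the planned 5 to 10%, and less well at 126 or 130.
- A reader might also infer that 116 is inconsistent with a 10% loss, because 130 less 10% is 117 and 126 less 10% is 113.4. But 65 per group less 10% is 58.5, or 58 whole patients per group, which makes 116.

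**Conclusion.** The statement of 80% power for d = 0.5 with 116 patients is wrong as written. The figure is 76%, a shortfall of about 4 points. The anxiety and depression figures are attainable within the planned attrition, but at about 122 to 124 patients. At the 116 named in the same paragraph they fall about 2 points short.

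The first conclusion rests on a two-sample comparison with equal groups and a two-sided 5% level, all taken from the article. The second also assumes that the same test lies behind the 80% and 92%. The article does not give the sample size for that sentence, so about 124 is inferred from the fit.

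This is a minor point. It does not show that the trial is too small for its purpose: the primary calculation stands, the tissue mediators have practically 80% power, and the detectable effect at twelve months moves only from 0.50 to about 0.525.

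**What to change.** Restate the secondary-outcome power so that each figure carries its sample size. Suggested wording:

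*With 116 patients (about 10% loss), power is 76% for d = 0.5, or 80% for d ≥ 0.525; it is 78% for anxiety (d = 0.51) and 90% for depressive symptoms (d = 0.61).*

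Alternatively, keep 80% and 92% for anxiety and depression and say that they assume about 124 patients (5% loss). In either case, treat tissue mediators separately: about 126 patients, with 79.5% power at d = 0.5. If the authors relied on baseline adjustment, they should state the assumed correlation and limit the claim to outcomes that have a baseline measurement.

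The cost is wording only, and the stated power becomes slightly less favourable. No patients are added (enrolment of all 130 is reported complete), and no analysis changes.

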### Quality of life and psychosocial functioning

PCa and its treatment are associated with significant psychological distress. Large-scale epidemiological studies on psychological disorders in the context of PCa are sparse. Nonetheless, in a study conducted by our team in 861 patients treated for PCa, we found that 17.0% exhibited clinical levels of depression, while 23.7% of the patients had clinical levels of anxiety [47]. Moreover, we observed sexual difficulties, sleep impairments and fatigue in 70.5%, 31.9%, and 18.5% of the patients, respectively.

Epidemiological studies have shown associations between a greater annual fish intake and lower depression rates [48–50]. A RCT conducted in medical students (with no psychiatric disorder), comparing a 12-weeks LCn3 supplementation to a placebo, showed a 20% reduction of anxiety symptoms [51]. A recent study found no significant effect of omega-3 supplementation on sleep quality [52], while a study of 633 breast cancer survivors showed that a higher intake of omega-6 relative to omega-3 was associated with a higher risk of fatigue [53]. These questions remain to be investigated in PCa patients using a RCT.

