### Randomization/concealment/blinding

Patients will be randomized to the intervention or placebo group 6 weeks (acceptable range 4 to 10 weeks) prior to RP. Randomization will take place at the preoperative appointment or an appointment taken specifically for the study. The randomization process will consist of a computer-generated random listing of the treatment arm using a 1:1 allocation. The randomization will be generated by the Clinical research oncology pharmacy, using permuted random blocks of 2 to 8. Patient allocation information will be kept in a binder in a locked room of the pharmacy for the entire study period. Patients, as well as all study personnel, including outcome assessors, and medical doctors will be blinded to treatment allocation and block sizes.

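### The 92% power for depressive symptoms rests on an effect size from patients treated for depressive disorders, which is not supported as the expected difference in men not selected for depression

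*Protocol article*

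**What the plan says.** All the power statements for secondary outcomes are in the Protocol article, Sample size calculation.

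- General statement: "A total sample size of 116 will provide 80% statistical power to detect a moderate or large effect size (≥0.5").
- Extension to patient-reported outcomes: "This sample size will also be sufficient to detect expected between-groups differences on quality of life dimensions". The next sentence supports this with two borrowed effect sizes, d = 0.51 for anxiety and d = 0.61 for depression. The source of the second is given as: "it yielded a moderate effect size (d = 0.61) for treating depressive disorders (vs. placebo) in another [72".
- Resulting figure: "a power of 92% to detect an effect for depressive symptoms", conditional on those effect sizes in the final sample.
- Attrition: "we expect a 5 to 10% loss to follow-up, which will affect only secondary outcomes".

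The Inclusion criteria and Exclusion criteria sections select on age, consent, choice of prostatectomy and Gleason score. They set no depression threshold, and the only psychiatric exclusion is bipolar disorder. The Background section on quality of life and psychosocial functioning reports the team's own survey of 861 treated patients: "we found that 17.0% exhibited clinical levels of depression, while 23.7% of the patients had clinical levels of anxiety [47". The statistical analysis of secondary outcomes uses linear mixed models for quality of life and does not restrict any comparison to men with depression.

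**The concern.** A standardised effect seen when treating a depressive disorder describes people who entered treatment with that disorder. This trial compares mean HADS depression scores across all randomised men, most of whom, on the article's own proxy figure, would not have clinical depression. The article gives no argument for carrying 0.61 over to them, yet uses it to support the claim that the sample suffices for the differences expected here.

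What is at stake is interpretation. HADS depression is a named secondary outcome with its own published power. If the comparison shows no difference, a reader who takes 92% at face value may give that result more weight than the design supports.

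**Working it through.** **Inputs**

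- d = 0.61 (depression), d = 0.51 (anxiety), 116 men in total, 5 to 10% loss from 130: Sample size calculation.
- Two-sided 0.05: "For all analyses, bilateral *p*-values of less than 0.05 will be considered statistically significant" (Statistical analyses, Primary outcome).
- Equal groups: "using a 1:1 allocation" (Randomization/concealment/blinding).
- 17.0% with clinical depression: Background, quality of life and psychosocial functioning.

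**Formula.** Two-sample t-test with n per group. The noncentrality is d × √(n/2), and power comes from the noncentral t distribution with 2n − 2 degrees of freedom.

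**Step 1: reproduce the stated figures**

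A 5% loss leaves 130 × 0.95 = 123.5 men, about 62 per group. A 10% loss leaves 117, close to the stated 116 (58 per group).

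| n per group | d = 0.61 | d = 0.51 | d = 0.50 |
|---|---|---|---|
| 62 | 92.1% | 80.4% | 78.9% |
| 58 | 90.3% | 77.7% | 76.1% |

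At n = 62 and d = 0.61 the noncentrality is 0.61 × √31 = 3.40. At n = 58 it is 0.61 × √29 = 3.28. The stated 92% and 80% therefore both fit about 123 men. With the 116 named in the same paragraph, power is about 90% at 0.61 and about 76% at 0.5. Power of 80% is reached at d = 0.525.

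**Step 2: power at smaller effects, 58 per group, simple two-group comparison**

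| d | Power |
|---|---|
| 0.4 | 57% |
| 0.3 | 36% |
| 0.2 | 19% |

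**Step 3: what 0.61 requires in this population**

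The article gives no d for unselected men, so this step is an illustration under assumptions. Suppose 17% of men respond at 0.61, the other 83% respond at d_n, and the SD is the same in both. The average effect is 0.17 × 0.61 + 0.83 × d_n.

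| Assumed d_n | Average d | Power (58 per group) |
|---|---|---|
| 0.2 | 0.27 | 30% |
| 0.4 | 0.44 | 64% |
| 0.5 | 0.52 | 79% |
| 0.61 | 0.61 | 90% |

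Under this mixture, the stated power is recovered only if men without clinical depression respond as strongly as patients treated for a depressive disorder.

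**Step 4: allowance for the planned model**

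HADS is measured at baseline and at four follow-up visits (Table 1). As an assumption, take a correlation of 0.5 between any two visits.

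- Baseline-adjusted comparison at 12 months: residual variance 1 − 0.5² = 0.75. Power at d = 0.4, 0.3 and 0.2 is 69%, 46% and 23%.
- Baseline-adjusted average of four visits: residual variance (1 + 3 × 0.5)/4 − 0.5² = 0.375. Power is 94%, 74% and 42%.

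The Step 2 figures are therefore not the power of the planned analysis, which may be higher. Neither the correlation nor the contrast is given in the article.

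**The case against.** The article is open about its source. It says that 0.61 comes from treating depressive disorders and gives the power as conditional on that effect, and the arithmetic reproduces. All of this stands. What remains is the word expected and the claim of sufficiency, which turn a conditional calculation into a statement about this trial.

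The power figures at smaller effects are for a single unadjusted comparison, and the mixed model could do considerably better (Step 4). This also stands and must be said alongside them. It does not make 0.61 the right effect for this population.

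Three stronger readings are tempting and are not supported:

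- **That real power is only 8 to 9%.** This is Step 3 with d_n = 0 (average d of 0.10). It needs exactly no effect in 83% of men. It is the floor of that illustration, not a realistic estimate. The article itself cites d = 0.51 for anxiety in medical students without psychiatric disorder. That is a different symptom in a different population, but it is a moderate effect in a non-clinical sample.
- **That the other 83% have little room to improve.** The 17.0% reflects a clinical threshold in men already treated, while the outcome is a continuous score. Men below a threshold can have symptoms, and they can worsen after surgery, so a difference could come from preventing deterioration.
- **That the anxiety figure has the same fault.** Its source sample had no psychiatric disorder, so this objection does not reach it.

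Finally, this is one of many secondary outcomes, and no passage plans to read a null result as evidence of no effect. That is fair, and it limits the point to a correction of wording.

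**Conclusion.** The point holds as a statement about the source of the effect size, not about the arithmetic. The 92% is correct for about 123 men at d = 0.61 (about 90% with 116). However, 0.61 belongs to patients treated for depressive disorders and is not supported as the expected difference in men who are not selected on depression. The article should not present 92% as this trial's power for HADS depression.

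With 116 men in a simple two-group comparison, the smallest effect detectable with 80% power is d of about 0.52. Power at the stated 0.5 is about 76%, and at 0.4, 0.3 and 0.2 it is 57%, 36% and 19%. These figures assume 58 per group, equal SDs and two-sided 0.05, and the planned model may raise them.

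The true effect in this population cannot be derived from the article, so no single replacement power can be given. The 17.0% is a proxy from treated men, but the mismatch does not depend on its exact value, because entry does not depend on depression. The total of 130 is set by Ki-67 and is unaffected, as is the primary analysis.

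**What to change.** In Sample size calculation:

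1. Withdraw, for depressive symptoms, the statement that the sample suffices for the expected between-group differences.
2. Say that the 92% applies only if unselected men respond as strongly as patients with depressive disorders, and that it corresponds to about 123 men (about 90% with 116).
3. State that 116 men give 80% power for d of about 0.52 in a simple two-group comparison, in place of 0.5, where power is about 76%. Add the power at 0.4, 0.3 and 0.2 (57%, 36% and 19%).
4. Note that the planned mixed model with baseline and repeated measures may raise these powers.

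The cost is wording only. The stated figure becomes less favourable, and no patients, visits or analyses change. With enrolment complete, the correction bears on how the depression result is read, so it should be made before that result is reported.

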### Statistical analyses

#### Primary outcome

The average proportion of cells expressing Ki-67 in each group will be compared, using the t-test, after transformation of the data if the population is not normally distributed. The Wilcoxon rank sum test will be used if observations are not normally distributed after transformation procedures. Multivariable linear regression will be carried out in the event of unbalanced distributions of important baseline characteristics such as cancer grade and stage, age, baseline inflammatory levels, diet or health behaviors. The intervention leading to the primary outcome is of a relatively short duration (4–10 weeks) and since almost all recruited patients are expected to undergo prostatectomy, few missing data are expected. The analyses will include all randomized patients for whom a ki-67 is measurable.

A *per protocol* analysis will also be carried out as exploratory analyses. These analyses will include participants with a measurable ki-67 and who will have taken at least 80% of intervention or placebo doses.

For all analyses, bilateral *p*-values of less than 0.05 will be considered statistically significant.

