#### Secondary outcomes

For the secondary outcome pertaining to prostatic levels of inflammation mediators, the t-tests (or Wilcoxon rank-sum test) will be used to compare levels across groups.

Blood levels of inflammation biomarkers as well as outcomes concerning quality of life are measured at multiple time points. For these analyses, linear mixed models, to take into account for multiple measurements, will be performed.

Confounding factors will also be taken into account in the analyses in the case of unbalanced distribution between groups.

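### The primary Ki-67 analysis adjusts for baseline factors only if they look unbalanced and lets normality checks choose the scale, which forgoes precision and leaves the primary effect measure unfixed

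*Protocol article*

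**What the plan says.** Under Statistical analyses, Primary outcome, the protocol article compares mean Ki-67 proportions by t-test and transforms the data only if they are not normal; the transformation is not named. It continues: "The Wilcoxon rank sum test will be used if observations are not normally distributed after transformation procedures". On covariates it says: "Multivariable linear regression will be carried out in the event of unbalanced distributions of important baseline characteristics such as cancer grade and stage"; the list goes on to age, baseline inflammatory levels, diet and health behaviours. It gives no criterion for normality or imbalance, and it does not say whether the regression replaces the unadjusted test or stands beside it. The 0.05 threshold applies to every analysis.

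The Sample size calculation section uses a single analysis: "Sample size analysis was done using a two-sample t-test for a log-normal geometric mean ratio".

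For the secondary outcomes the imbalance rule returns: "Confounding factors will also be taken into account in the analyses in the case of unbalanced distribution between groups".

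**The concern.** Two decisions in the primary analysis wait for the data.

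- **Covariates.** In a properly randomised trial, baseline imbalance is chance and is a poor reason to adjust. A covariate earns its place by predicting the outcome, and a prognostic covariate improves precision whether or not the arms happen to differ on it. The Randomization section names no stratification factor and eligibility is Gleason score 7 or above, so tumour grade is an obvious candidate.
- **Scale and test.** Depending on the branch, the primary result is a difference in means, an effect on some transformed scale, or a rank comparison. Only one of the possible transformations, the log, gives the geometric mean ratio on which the trial was sized.

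At stake are precision, a primary effect measure that is known in advance, and clarity about which p-value is the primary one.

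**Working it through.** **Inputs from the Sample size calculation section.** Two-sided alpha 0.05; "we assume a coefficient of variation of 0.4"; a ratio of 0.8; and "a total of 126 patients (63/group) will provide 90% power".

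**1. Reproduce the plan's figure.** Log-scale SD = √ln(1 + 0.4²) = 0.3853. Log-scale difference = |ln 0.8| = 0.2231. Then n per group = 2 × (1.960 + 1.282)² × (0.3853/0.2231)² = 62.6, so 63. Power at 63 per group is 90.2% by the normal approximation and 89.7% by the noncentral t. Inflating 126 for 3% dropout gives 130. The sample size is right, on the log scale. On the raw scale, a 20% difference with SD equal to 0.4 of the control mean in both arms (an assumption) would need 85 per group.

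**2. What adjustment can give.** The residual SD becomes 0.3853 × √(1 − R²), where R² is the share of log Ki-67 variance explained by baseline covariates. The article gives no R², so a range is assumed. The normal approximation charges nothing for estimating the covariates:

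| Assumed R² | Power at 63/group | n/group for 90% |
|---|---|---|
| 0 | 90.2% | 63 |
| 0.1 | 92.9% | 57 |
| 0.2 | 95.3% | 51 |
| 0.3 | 97.3% | 44 |

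**3. Simulated power, fixed against triggered adjustment** (63 per group, log-normal outcome, ratio 0.8).

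- Four covariates, 4000 runs per setting: fixed adjustment gives about 92, 94 and 97% at R² = 0.1, 0.2 and 0.3. Imbalance-triggered adjustment gives about 90 to 92% over the same range. At R² = 0 fixed adjustment loses about 1 point.
- Six independent covariates, 4000 runs per setting, with unbalanced taken to mean baseline p < 0.05 (an assumed rule, since the article gives none):

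| Assumed R² | Unadjusted log t-test | Triggered | Fixed adjustment |
|---|---|---|---|
| 0 | 89.6% | 89.2% | 88.5% |
| 0.2 | 89.8% | 90.3% | 94.3% |
| 0.4 | 89.4% | 90.6% | 98.1% |

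At R² = 0.2 fixed adjustment gains 94.3 − 89.8 = 4.5 points and the trigger gains 90.3 − 89.8 = 0.5. At R² = 0.4 the gains are 8.7 and 1.2 points. The trigger therefore recovers about one ninth to one seventh of what is available.

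**4. How often chance pulls the trigger.** With six independent covariates tested at 0.05, 1 − 0.95⁶ = 26.5%; the simulations gave 26 to 28%. In about a quarter of valid trials the primary model would change for no reason but chance.

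**5. Type I error of the rule as written** (six covariates, 8000 null runs per setting; non-normal taken to mean Shapiro-Wilk p < 0.05 on pooled residuals, and the unnamed transformation taken to be the log). The normality sequence alone gives about 5.2%. With triggered regression as the replacement test the rate is 5.2, 4.5 and 4.0% at R² = 0, 0.2 and 0.4. If either the unadjusted or the triggered result could be claimed, it is 5.5 to 5.7%.

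**The case against.** The order of tests is written down in advance, and only one step of it applies to a given data set. A reader might infer from the several branches that the false-positive rate is materially raised. That would require running all the tests and reporting the smallest p-value, which the article does not describe; step 5 shows that the rule as written stays near or slightly below 5%. This objection stands.

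A reader might also infer that the trial falls short of its planned power. It does not: the unadjusted log-scale t-test delivers about 90%. What is at issue is a forgone gain, and its size rests on an R² that the article does not supply. The Background and Fig. 1 describe an intermediate-risk population, which could narrow the range of grade and so its prognostic value. This also stands.

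If Ki-67 is close to log-normal, the raw-scale branch would rarely be taken, so in practice the result would usually be on a transformed scale. That weakens the complaint about the effect measure but does not remove it: the transformation is unnamed and the fallback is a rank test.

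Finally, one might read the secondary-outcome text as ignoring baseline values in the mixed models. The Secondary objectives state those effects relative to baseline, and how baseline enters such a model is something an article commonly leaves to the full protocol or SAP. That reading is not supported.

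What the objections do not reach is the rule itself. Adjustment triggered by imbalance is stated in the article, not left open, and it is a poor rule.

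**Conclusion.** The point holds as one of efficiency and clarity, not of validity. The primary analysis should be one fixed log-scale model. Over an assumed R² of 0.1 to 0.3, the imbalance trigger gives up about 2 to 5 points of power compared with fixed adjustment (92, 94 and 97% against roughly 90 to 92%); at R² = 0 fixed adjustment costs about 1 point. The sample size is sound and need not change. The article also leaves open which of the adjusted and unadjusted results is primary, and lets the data settle whether the headline is the geometric mean ratio on which the design rests.

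The figures assume a log-normal outcome, independent covariates, and particular definitions of imbalance and non-normality, because the article defines neither. The direction of the comparison depends only on the covariates having some prognostic value.

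**What to change.** Before unblinding, state one primary analysis: linear regression of log Ki-67, with a stated rule for zero values, on arm plus a short fixed list of pre-randomisation factors such as biopsy grade, clinical stage, baseline PSA and age, whatever balance is observed. Report the adjusted geometric mean ratio with its 95% CI. Keep the unadjusted log-scale t-test and the Wilcoxon test as sensitivity analyses, and say that neither can displace the primary result.

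Specify biopsy grade. The Confounding variables section lists both clinical and pathological grade, but grade read from the surgical specimen is obtained after the intervention has begun and should not be a covariate.

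In the secondary-outcome section, replace the imbalance trigger with pre-specified covariates.

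The cost is wording, a few degrees of freedom, and about 1 point of power if the covariates turn out not to be prognostic. The data are already scheduled for collection at baseline (Table 1 and Confounding variables), so no patients or visits are added.
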